### Control

This is a school-as-usual condition. As such, students can access the school counsellor as needed and are permitted to participate in any mental health education or activities initiated by the school or external mental health professionals. Schools allocated to the control condition are placed on a wait list to receive the Smooth Sailing service after the trial data collection period has been completed.

### Procedure

At baseline, researchers from the Black Dog Institute visit the school to conduct the study during class time. After providing a verbal explanation of the study and confirming consent, students are asked to use any internet device to visit the study website. Instructions for registering and completion of study questionnaires are provided to students on paper. The researchers remain with students to provide assistance and answer any questions. At 6 weeks and 12 weeks, researchers revisit the schools and repeat this process. Students who are unable to access the website at 6 weeks or 12 weeks because of technical issues are given a paper copy of the questionnaires to complete. If these students are the intervention arm, researchers use a paper scoring method to calculate participants’ step at these timepoints and inform the school counsellor verbally if the student requires follow-up. The research team then enters these responses into the system on return to the office resulting in the immediate update of the Web-based portal. Researchers meet with the school counsellor after each visit to review the students who require follow-up and to ensure that counsellors feel adequately supported to conduct these. The researchers contact the school counsellors 2 working days after each visit to review student follow-ups and monitor any adverse events.

**Table 4 table4:** Stepping decisions at 6 weeks and 12 weeks.

Current step (symptom severity: score range)	Previous step				
	0	1	2	3	4
0 (Minimal: 0-4)	0	1	2	3	4
1 (Mild: 5-9)	1	1	2	3	4
2 (Moderate: 10-14)	2	2	3	3	4
3 (Moderately severe: 15-19)	3	3	3	4	4
4 (Severe: 20+)	4	4	4	4	4

### Sample Size

The target sample size for this trial is 1600. This calculation is based on detecting an effect size of 0.20, which is similar to that obtained in previous school-based depression intervention research [9]. The statistical power level is set at 0.8, alpha=.05 (2-tailed), whereas a correlation of 0.5 is assumed between the scores at baseline and endpoint. A design effect is calculated assuming an intraclass correlation of 0.02 and an average school sample of 300 students to allow for possible clustering effects. This estimate was derived from previous Australian school–based studies [9]. The estimated sample size also accommodates for a 20% attrition rate based on previous school-based trials [43]. To achieve the desired sample size and ensure representation from a range of different types of schools, the target is set at 16 schools with approximately 100 students participating per school.

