## Results

The results for this trial are currently under analysis. Ethics approval was provided by UNSW HREC on November 24, 2017, and by the NSW Department of Education SERAP on January 10, 2018. An Expression of Interest for the trial was advertised through the NSW School-Link Initiative (School-Link) newsletter and email. We were subsequently contacted by a school representative (eg, School Counsellor, Head of Well-Being) from 88 different schools. Throughout January and February 2018, 22 secondary schools across NSW agreed to participate in the trial. These schools were randomized into 2 conditions, with 10 schools assigned to receive the intervention and 12 assigned to the control condition. The first baseline assessment occurred on February 22, 2018, with the 12-week endpoint assessments completed on Friday, June 29, 2018. Control schools are currently receiving the service, due for completion by June 30, 2019.

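### The target of 1600 students does not follow from the stated sample-size inputs, and the 300 students per school in the design effect contradicts the planned 100

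*Protocol article*

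**What the plan says.** The Sample Size section of the protocol article opens with the total: "The target sample size for this trial is 1600". It then lists the inputs. "This calculation is based on detecting an effect size of 0.20"; power is 0.8 with a two-tailed alpha of .05; and "a correlation of 0.5 is assumed between the scores at baseline and endpoint". The design effect is computed "assuming an intraclass correlation of 0.02 and an average school sample of 300 students". An allowance of 20% is made for attrition. The paragraph ends with the layout: "the target is set at 16 schools with approximately 100 students participating per school". The Abstract repeats 1600 students, 16 schools and about 100 per school.

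The Results section reports that 22 schools were randomised, "with 10 schools assigned to receive the intervention and 12 assigned to the control condition". It gives no number of students. The Analysis section plans a mixed-effects repeated-measures model with school as a random effect. The administration schedule (Table 5) shows the primary outcome measured at baseline and 12 weeks only.

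**The concern.** Two things look wrong in one paragraph. The cluster size behind the design effect is three times the size planned, and nothing reconciles the two: at 300 per school, 1600 students would come from five or six schools, not 16. And a design effect for 300 at ICC 0.02 is close to 7, which is hard to square with a total of only 1600.

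This is the only power justification given for the primary outcome. If the stated 80% for 0.20 SD is not what the inputs deliver, a null result on help-seeking intentions could be read as stronger evidence against an effect of that size than the design supports.

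**Working it through.** **Inputs (Sample Size section).** Effect d = 0.20; power 0.80; two-sided alpha 0.05; correlation r = 0.5; ICC 0.02; cluster size m = 300 (design effect) or 100 (layout); attrition 20%. Equal allocation and equal school sizes are my assumptions. The article does not say how r enters, so both usual readings are shown: change score, variance factor 2(1 − r) = 1; baseline-adjusted, factor 1 − r² = 0.75.

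**Step 1: total without clustering.** N = 4 × (1.96 + 0.8416)² / 0.20² × factor = 785 (change score) or 589 (baseline-adjusted).

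**Step 2: try to reproduce 1600.** Multiply by DE = 1 + (m − 1) × 0.02 and divide by 0.8 for attrition.

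| m | DE | Change score | Baseline-adjusted |
|---|---|---|---|
| 300 (stated) | 6.98 | 6,848 | 5,136 |
| 100 (planned) | 2.98 | 2,924 | 2,193 |
| 80 (planned, after attrition) | 2.58 | 2,531 | 1,898 |

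No row gives 1600. Other variants at m = 300 fail too: inflating by 1.2 instead of dividing by 0.8 gives 6,574 or 4,931, and a one-sided alpha gives 5,410 or 4,049. Leaving clustering out gives 785/0.8 = 981 or 589/0.8 = 736. Averaging two follow-ups is not available, because the primary outcome is not measured at 6 weeks.

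**Step 3: power of the planned layout.** 16 schools, 8 per arm, 80 analysed in each, so 640 per arm and DE 2.58. SE = √(factor × 2.58 × 2/640) = 0.0898 (change score) or 0.0778 (baseline-adjusted). The noncentrality 0.20/SE is 2.23 or 2.57.

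- Normal approximation: 61% or 73%.
- Noncentral t on 16 − 2 = 14 df: 55% or 67%.
- Effect detectable with 80% power on 14 df: 0.27 or 0.23 SD.
- With no attrition at all (100 analysed per school, DE 2.98): 64% or 76% by normal approximation.

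**Step 4: sensitivity to school-level correlation.** Step 3 applies ICC 0.02 unchanged to change or adjusted scores, which amounts to school means correlating 0.5 over time. Suppose instead that they correlate ρ, with 0.5 kept within schools. The correlation of observed school means is then (80 × 0.02/2.58) × ρ + (0.98/2.58) × 0.5, and it replaces r in the variance factors.

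| ρ | Correlation | Factors (change; adjusted) | Power on 14 df | Normal approximation |
|---|---|---|---|---|
| 0.7 | 0.624 | 0.752; 0.611 | 67%; 76% | 73%; 81% |
| 0.8 | 0.686 | 0.628; 0.529 | 74%; 81% | 80%; 86% |

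The article states no value of ρ.

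**Step 5: the 22 schools randomised (10 vs 12), 20 df.** Student numbers are assumed, with ICC and factors as in Step 3.

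- 1600 recruited in total: 1,280/22 = 58.2 analysed per school, DE 2.14, noncentrality 2.43 or 2.81, power 64% or 76%.
- 100 recruited per school: 80 analysed, DE 2.58, noncentrality 2.60 or 3.00, power 70% or 82%.

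**The case against.** **300 is conservative.** A reader might infer that power is lost because 300 was assumed and 100 planned. The arithmetic does not support that. The larger cluster size inflates the design effect (6.98 against 2.98), so correcting it to 100 lowers the requirement. The contradiction and the shortfall are separate faults. The 5,140 to 6,850 figure shows that the calculation does not reproduce; it does not describe a layout anyone planned.

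**The trial as run may be adequately powered.** This stands. A reader might conclude that the completed trial was underpowered, but the article gives no student numbers. The range in Step 5 runs from 64% to 82% depending on recruitment and analysis. Nor is having 22 schools instead of 16 an error: 16 was a target and 22 was achieved, and more schools help.

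**School means may be stable over time.** This also stands as a caveat. With ρ at 0.7 or 0.8, the baseline-adjusted power of the planned layout reaches or approaches 80%. But that rests on an input the article does not state, so it cannot be the basis of the printed 1600.

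**300 may be a misprint.** With 30 per school the change-score calculation gives 785 × 1.58/0.8 = 1,550, close to 1600; with 60 the baseline-adjusted one gives 1,604. Neither size appears in the document, either would still contradict 100, and the power of the planned layout would be unchanged. The explanation is conjecture.

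**Conclusion.** The point holds as an error in the printed calculation. The target of 1600 cannot be reproduced from its stated inputs under either reading of the 0.5 correlation, at the stated cluster size or the planned one. The stated size gives more than three times the target; the planned one gives about 1.2 to 1.8 times, depending on the reading and on whether the design effect uses 80 or 100.

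On the stated inputs the planned layout falls moderately short of 80% power, by 7 to 19 percentage points on the normal approximation and 13 to 25 on 14 df. That shortfall assumes equal school sizes and an ICC that carries over unchanged to change or adjusted scores. Unequal school sizes would lower power; stable school means would raise it. The documents do not support a categorical statement about the power of the trial as run.

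**What to change.** Rewrite the Sample Size paragraph so that it:

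- uses one cluster size, consistent with the design, in both the design effect and the layout;
- says how the 0.5 correlation enters (change score or baseline adjustment) and whether the ICC applies to raw or adjusted scores;
- restates power for 0.20 SD, or the detectable effect, for the 10 and 12 schools randomised, with realised students per school and between-school degrees of freedom.

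No single replacement power or detectable effect should be inserted until the realised numbers are used, since the Step 5 figures rest on assumed recruitment. If ρ is given a value, its source should be stated.

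The cost is one paragraph and a short recalculation. Data collection is complete, so enrolment, the outcome and the analysis do not change. The restated power may turn out less favourable than 80%, and a null result should be interpreted through its confidence interval with that figure beside it.

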### Outcome Measures

The administration schedule for the outcome measures (Multimedia Appendix 1) is outlined in Table 5.

#### Demographics

At baseline, students provide their name, email, mobile phone number (optional), gender, and date of birth. Students are asked to report their current employment status (answered part-time, casual, or nil) and whether they identify as Aboriginal and or Torres Strait Islander (answered yes, no, I’d rather not say) or Lesbian, Gay, Bisexual, Trans or Intersex (answered yes, no, I’d rather not say).

#### Mental Health History

At baseline, participants are asked to report whether they have ever known someone with a mental illness (answered yes, no, I’m not sure); cared for someone with a mental illness (answered yes, no, I’m not sure); or if they have previously had a session with the school counsellor at their school (answered yes, no, I’d rather not say). Participants are also asked if they have ever used the internet to find information about a mental health problem (answered yes, no, I’m not sure) and whether they think doing a Web-based program will help their mental health (answered yes, no, I’d rather not say). At baseline, 6 weeks, and 12 weeks, participants are also asked if they have been diagnosed with a mental health problem or mental illness, if they have received any treatment for a mental health problem or mental illness, or if they have taken any prescribed medication (eg, antidepressants) for a mental health problem or mental illness (answered yes, no, I’d rather not say).

### Primary Outcome Measure

#### General Help-Seeking Questionnaire

The General Help-Seeking Questionnaire (GHSQ) is used to measure help-seeking intentions. Participants are asked to rate how likely they are to seek help from 13 different sources (friend, partner, parent, other family member, teacher, other adult, school counsellor, doctor/general practitioner, mental health professional, telephone helpline, mental health website, a Web-based mental health program, and other internet activity) if faced with a mental health problem, with each item answered on a 5-point scale ranging from extremely unlikely to extremely likely [27]. Participants can also indicate if they would not seek help from anyone at all or if they would seek help from someone not listed. The GHSQ has demonstrated satisfactory psychometric properties for measuring the likelihood of seeking help among adolescents [27]. In this study, a *total help-seeking intentions score* is calculated for each participant consisting of their responses to the 13 sources, with total possible scores ranging from 14 to 70.

**Table 5 table5:** Outcome measures administration schedule.

Assessment		Construct	Baseline	6 weeks	12 weeks
**Primary outcome**					
	General Help-Seeking Questionnaire	Intentions to seek help	Yes	No	Yes
**Secondary outcomes**					
	Actual Help-Seeking Questionnaire	Actual help-seeking behavior	Yes	Yes	Yes
	Generalized Anxiety Disorder Questionnaire	Generalized anxiety	Yes	Yes	Yes
	Center for Epidemiologic Studies Depression Scale—Child Version	Depressive symptoms	Yes	Yes	Yes
	Functioning	Functioning	Yes	Yes	Yes
	Distress Questionnaire-5	Psychological distress	Yes	Yes	Yes
	Barriers to Adolescents Seeking Help-Brief	Barriers to seeking help	Yes	No	Yes
	Mental Health Literacy and Stigma Scale	Mental health literacy and stigma	Yes	No	Yes
**Tertiary outcome**					
	Satisfaction questionnaire^a^	Service adherence and satisfaction	No	No	Yes

^a^Delivered to Intervention schools only.

### Secondary Outcome Measures

#### Actual Help-Seeking Questionnaire

The Actual Help-Seeking Questionnaire is used to assess help-seeking behavior [44]. Using the same sources presented in the GHSQ, participants are asked to report whether they have sought help for a mental health problem from these sources in the past 6 weeks (answered yes or no). Participants can also indicate if they have sought help from someone not listed. An additional question asks participants whether they have needed support for their mental health but did not seek help. The use of this questionnaire in youth has been well supported [30]. In this study, participants’ responses at baseline and 12 weeks posttest are categorized into a new variable named *help-seeking from adults*. Participants who have sought help from any adult source are categorized as yes, with those who have not categorized as no. This variable is then used as a secondary outcome for analyses, alongside the number of participants who report not seeking help at all despite having a need for mental health support.

#### Generalized Anxiety Disorder Questionnaire

Generalized anxiety is measured using the GAD-7 [22], which is a brief measure of anxiety consisting of 7 items that are rated on a scale from not at all (0) to nearly every day (4). Total scores can be classified as nil to mild (5-9), moderate (10-14), or moderately severe to severe (>15). A score of 10 and above is recommended as a reasonable cutoff point for identifying cases of clinical anxiety [22]. The GAD-7 has been found to have good test-retest reliability and strong criterion validity [22].

#### Center for Epidemiologic Studies Depression Scale—Child Version

The Center for Epidemiologic Studies Depression Scale (CES-D) was originally developed for measuring depression in an adult population [45] and was later modified into the child version, the Center for Epidemiologic Studies Depression Scale – Child Version (CES-DC) [46]. It is comprised 20 items, rated from not at all (0) to a lot (3), with 4 items reverse-scored. The total possible scores range from 0 to 60, with higher scores indicative of increased levels of depression. The scale has been found to have good psychometric properties among adolescents [47]. The most commonly used cutoff score for the CES-D is 16 and above, which indicates the individual should be further screened for risk of depression [48].

#### Distress Questionnaire-5

The Distress Questionnaire-5 (DQ5) is a brief, valid screener used for identifying those at risk of psychological distress in the general population [49]. The DQ5 consists of 5 items rated from never (1) to always (5). Total scores range from 5 to 25 and higher scores indicate greater psychological distress. It has been suggested that the DQ5 may be superior to the K6 and K10 in identifying increased risk for common mental disorders, with a screening cutoff point of 11 indicating the likely presence of a mental health condition [49].

#### Functioning

Taken at baseline and posttest, this is a 1-item question in which students are asked to rate how difficult their symptoms of anxiety and depression have made their daily life and relationships. Participants answer using a 4-point Likert scale ranging from not at all difficult (0) to very difficult (4).

#### Barriers to Adolescents Seeking Help

The Barriers to Adolescents Seeking Help-Brief [50] is a shortened (11 items) version of the original questionnaire, measuring barriers to help-seeking behavior among adolescents. Participants rate their level of agreement with a list of statements about help-seeking from strongly disagree (1) to strongly agree (6). Total scores range from 11 to 66, with higher mean scores reflecting greater resistance to seeking professional help. The scale has been found to have good test-retest reliability and validity in a population of high school students [50].

#### Mental Health Literacy and Stigma Scale

This scale measures a person’s confidence about help-seeking for mental health and stigmatizing attitudes toward mental illness. It has demonstrated good internal and test-retest reliability and validity [51]. A shortened version of the questionnaire, consisting of 4 items assessing confidence seeking help and 9 items assessing stigmatizing attitudes of mental illness, has been selected for use in this study. Item responses are rated on a 5-point scale from strongly disagree (1) to strongly agree (5) with 9 items reverse-scored. Total scores for this scale range from 13 to 65, with higher scores indicating greater confidence in seeking help for mental health problems and lower levels of stigma.

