### Hypotheses

The primary hypothesis is that those who receive the Smooth Sailing service will report higher scores of overall help-seeking intentions at 12 weeks posttest compared with baseline. The secondary hypothesis is that compared with students in the control condition, those assigned to intervention will report improved help-seeking behavior and reduced levels of depression, anxiety, distress, and barriers to care, as well as improved mental health literacy and stigma at 12 weeks posttest.

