### Analysis

Data are collected using the Black Dog Institute electronic health platform. Data will be downloaded into Microsoft Excel and exported to SPSS Version 22.0 (SPSS Inc) for analysis. Primary analyses will be undertaken on an intention to treat basis, including all participants randomized, regardless of treatment received. Effectiveness of Smooth Sailing will be established by a change in the GHSQ scores between baseline and 12 weeks using a mixed-effects model repeated-measures analysis. The school will be included in analyses as a random effect to evaluate and accommodate clustering effects. In analyses of scaled secondary variables, methods comparable with those of the primary analysis will be used. An analysis of covariance will be conducted for the secondary outcomes of anxiety, depression, distress, functioning, mental health literacy, and barriers to help-seeking, controlling for baseline scores. To determine the effect of the intervention on help-seeking, 2 binary logistic regression analyses will be used. In model 1, the dependent variable will be help-seeking from adults at 12 weeks. The baseline result will be entered at step 1 in the model, with the study arm entered at step 2. In model 2, the dependent variable will be not seeking help at all at 12 weeks despite a need. The baseline result will be entered at step 1, with the study arm entered at step 2.

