## Discussion

This study protocol outlines the Smooth Sailing trial, which aims to investigate the effectiveness of a Web-based mental health service for secondary school students. Using a randomized controlled design, this study evaluates the efficacy of the Smooth Sailing service for improving a range of mental health outcomes among students compared with school-as-usual. The service was designed to increase adolescents’ help-seeking intentions for mental health problems, as well as to improve help-seeking behaviors and reduce symptoms of anxiety, depression, and distress. This is critically important to this age group as mental illness first emerges during adolescence and help-seeking from professionals is low [2,3]. Most notably, this study represents the first attempt at delivering a school-based mental health service that incorporates the principles of stepped care with Web-based screening and intervention alongside direct face-to-face follow-up.

During the development of the service, school counsellors, parents, and general practitioners (GPs) outlined various concerns related to the accuracy, effectiveness, and suitability of the service for delivery in the school setting [18-20]. Some parents questioned the effectiveness of a Web-based service for determining the level of care their child required [20] and whether the service would increase stigma among students. Both parents and school counsellors were concerned that students may not openly disclose their symptoms to a Web-based service [18]. Parents, counsellors, and GPs [19] were also concerned about teens’ adherence and engagement with self-directed Web-based CBT programs. This study will be able to determine these outcomes. This trial will also evaluate the benefits of using a Web-based service to initiate school counsellor referrals for symptomatic students compared with traditional referral processes, and the capacity of school counsellors to manage these. This study will also be able to examine the effectiveness of school counselling services in Australia, an area in which effectiveness data are lacking.

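### The only score defined for the literacy and stigma scale adds 4 confidence items to 9 stigma items, so a change in it cannot be attributed to stigma

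*Protocol article*

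**What the plan says.** The section on the Mental Health Literacy and Stigma Scale describes a shortened version "consisting of 4 items assessing confidence seeking help and 9 items assessing stigmatizing attitudes of mental illness". Items are "rated on a 5-point scale from strongly disagree (1) to strongly agree (5) with 9 items reverse-scored". One score follows: "Total scores for this scale range from 13 to 65". The section then gives the direction of this single total as "with higher scores indicating greater confidence in seeking help for mental health problems and lower levels of stigma". No component score is defined.

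The Hypotheses section expects the intervention arm to show lower symptoms and barriers, "as well as improved mental health literacy and stigma at 12 weeks posttest". Table 1 assigns literacy and stigma together to this one scale. Table 5 lists no other outcome as a measure of stigma.

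The Analysis section states: "An analysis of covariance will be conducted for the secondary outcomes of anxiety, depression, distress, functioning, mental health literacy, and barriers to help-seeking", adjusted for baseline. Stigma is not named there.

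The Discussion reports several concerns raised while the service was being developed. One, from some parents, was "whether the service would increase stigma among students". After the list comes the sentence "This study will be able to determine these outcomes".

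**The concern.** The article makes two statements about stigma: a hypothesis that it will improve, and a claim in the Discussion that the trial can say whether it rises. Both rest on a single score that mixes stigma with confidence in seeking help.

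The two parts need not move together. The modules in Table 3 teach when and where to seek help, which bears on confidence. Screening and counsellor follow-up are features that could plausibly affect stigma differently, although the article offers no data on this.

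Two misreadings follow. A total near zero could be reported as no effect on stigma when the parts moved in opposite directions. A positive total could be reported as reduced stigma when only confidence rose.

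**Working it through.** **1. Reproduce the stated range.** Inputs from the scale's own section: 4 confidence items, 9 stigma items, each scored 1 to 5.

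- Confidence: 4 × 1 = 4 to 4 × 5 = 20 (span 16).
- Stigma: 9 × 1 = 9 to 9 × 5 = 45 (span 36).
- Sum: 4 + 9 = 13 to 20 + 45 = 65 (span 52).

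This matches the stated 13 to 65, so the score is the unweighted sum of both parts. That the 9 reversed items are the 9 stigma items is an inference, but the stated direction of the total requires it. Stigma's share of the span is 36/52 = 69%.

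**2. Offsetting in raw points.** With mean changes c per confidence item and s per stigma item (after reversal), the change in the total is 4c + 9s. It is zero when c = −(9/4)s = −2.25s.

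- A worsening of 0.11 per stigma item (−1.0) is offset by +0.25 per confidence item (+1.0).
- A worsening of 0.44 per stigma item (−4) is offset by +1.0 per confidence item (+4).

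So offsetting is point for point, but full cancellation always needs a larger per-item change in confidence.

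**3. Illustration in standardised units.** The article gives no component standard deviations or correlations, so these are assumptions: item SDs all 1, inter-item correlation ρ = 0.2 to 0.4, correlation r = 0 to 0.3 between components.

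- s_C = √[4(1 + 3ρ)] = 2.53 (ρ = 0.2) or 2.97 (ρ = 0.4).
- s_S = √[9(1 + 8ρ)] = 4.84 or 6.15.
- s_T = √(s_C² + s_S² + 2·r·s_C·s_S).
- Standardised effect on the total: d_T = (d_C·s_C + d_S·s_S)/s_T.

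For a true stigma worsening of d_S = −0.20:

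| Confidence effect d_C | Effect on total d_T |
|---|---|
| 0 | −0.16 to −0.18 |
| +0.20 | −0.08 to −0.09 |
| +0.30 | −0.03 to −0.05 |
| 0.20 × s_S/s_C = +0.38 to +0.41 | 0 |

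Attribution fails even when nothing cancels. A confidence-only gain of 0.20 gives d_T = 0.20·s_C/s_T = 0.08 to 0.09. A stigma-only improvement of 0.20 × s_C/s_S = about 0.10 gives the same total.

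**4. Power under the same assumptions.** From the Sample Size section: 1600 students, 20% attrition, ICC 0.02, baseline correlation 0.5, and the target of about 100 per school (that section also names 300 per school for the design effect, which is not used here).

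- Analysed per arm: 800 × 0.8 = 640; per school: 100 × 0.8 = 80.
- Design effect: 1 + 79 × 0.02 = 2.58; effective n per arm: 640/2.58 = 248.
- Residual SD: √(1 − 0.5²) = 0.866; SE = 0.866 × √(2/248) = 0.078.
- Stigma alone, d = 0.20: z = 0.20/0.078 = 2.57; power = Φ(2.57 − 1.96) = 73%.
- Total, with d_C = +0.30 and d_S = −0.20 (|d_T| = 0.034 to 0.050): power to detect worsening is 6% to 9%.

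**The case against.** Several points on the other side stand.

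- The Analysis section does not say that the total is what will be analysed. It names mental health literacy without specifying a score, and a fuller plan might score the components. But the scale's section positively defines the total and nothing else, and the Analysis list contains no stigma variable. Either the mixed total is analysed as literacy or stigma has no named analysis; neither reading answers the stigma question.
- A reader might infer that the protocol lists increased stigma as a harm it undertakes to test. It does not. The Discussion reports what some parents questioned, and the sentence promising an answer closes a list of several concerns. No objective or hypothesis tests for an increase. What stands is that stigma is on that list.
- A reader might also infer that a rise in stigma would be hidden. The documents do not show that. They give no evidence of opposite movement, and the hypothesis expects both to improve. The total is mostly stigma by range: under the assumptions above, a worsening of 0.20 with confidence unchanged still shows as 0.16 to 0.18. Erasing it needs a confidence gain of 0.38 to 0.41, about twice the 0.20 effect the trial was planned to detect. Partial masking needs less.
- The items measure students' own stigmatizing attitudes. The parents may have meant students being stigmatized for taking part. A separate stigma score would not answer that.

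**Conclusion.** The point holds in a limited form. With the one score the article defines, a change cannot be attributed to stigma or to confidence, and opposite movements would partly offset. The hypothesis on stigma and the Discussion's claim therefore go further than the defined score can support.

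The score arithmetic is certain: 4 to 20 plus 9 to 45, with stigma 69% of the span and a 2.25-fold per-item ratio for full cancellation. The standardised effects and the contrast of 73% with 6% to 9% power depend on assumed item SDs and correlations and on one chosen scenario. They show what could happen and do not estimate what will.

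This is a cheap improvement to a secondary outcome.

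**What to change.** In the scale's section, define two further scores from the same items: help-seeking confidence (4 items, 4 to 20) and stigma (9 items, 9 to 45, direction stated). In the Analysis section, name both as secondary outcomes, each analysed with the baseline-adjusted model already stated. The 13 to 65 total may be kept beside them.

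Base any statement on stigma on the difference in the 9-item score with its confidence interval. In the Discussion, limit the claim to students' own stigmatizing attitudes, since the items do not measure stigma experienced by participants.

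Cost: one or two more secondary tests, and a 4-item confidence score that is shorter and less reliable than the total. No new data are needed, and the primary outcome and sample size do not change.
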